### Clinical data collection

Comprehensive baseline data will be collected for all enrolled participants, encompassing the following categories:

Demographic characteristics: age, sex, height, and weight (with body mass index [BMI] calculated accordingly).

Stroke-related specifications: date of ischemic stroke onset, infarct location, history of reperfusion therapy (e.g., intravenous thrombolysis or mechanical thrombectomy), and related surgical interventions (e.g., decompressive craniectomy).

Comorbidities: presence of hypertension, diabetes mellitus, myocardial infarction, cardiomyopathy, and specific arrhythmias.

Current medications: use of antiplatelet agents, anticoagulants, statins, antihypertensive, and neurotrophic/neuroprotective agents.

Vital signs: body temperature, blood pressure, heart rate and rhythm, respiratory rate, and peripheral oxygen saturation.

Laboratory parameters: white blood cell count, neutrophil percentage, hemoglobin, platelet count, interleukin-6, C-reactive protein, procalcitonin, D-dimer, B-type brain natriuretic peptide, alanine aminotransferase, aspartate aminotransferase, serum creatinine, blood urea nitrogen, albumin, and prealbumin.

### Rehabilitation assessments

Rehabilitation assessments will be performed across multiple domains, including consciousness, cognitive and language function, motor and sensory function, swallowing ability, hemodynamic status, bladder and bowel function, activities of daily living, and psychological status. The following standardized instruments will be specifically utilized: the National Institutes of Health Stroke Scale (NIHSS) for neurological impairment (22, 23), the Fugl-Meyer Assessment (FMA) for motor function (24), the Berg Balance Scale (BBS) for balance function (25), the Modified Mann Assessment of Swallowing Ability (MMASA) for deglutition (26), and the Barthel Index (BI) for activities of daily living (27). Additionally, noninvasive hemodynamic parameters will be evaluated via an assessment system based on thoracic electrical bioimpedance (28, 29).

### Interventions

All participants will receive standard of care, consisting of conventional rehabilitation therapy and comprehensive nursing care. Specific interventions related to the study groups will be administered in addition to this baseline therapy.

Monitoring and Nursing Care: Participants will undergo continuous clinical observation and hemodynamic monitoring. Standardized nursing protocols will be implemented, including the management of indwelling catheters, anti-spasticity limb positioning, nutritional support, medication reconciliation, and psychological counseling.

Rehabilitation therapy: Personalized rehabilitation programs will be formulated by a multidisciplinary team, incorporating data from physical examinations, laboratory results, and functional assessments. Depending on clinical indications, therapeutic modalities may include acupuncture, Chinese therapeutic massage (Tuina), swallowing therapy, cognitive rehabilitation, and speech-language interventions. Neurological status and functional progress will be systematically reassessed to titrate treatment intensity and adjust rehabilitation plans accordingly.

Communication and education: To ensure treatment adherence, clinicians will provide structured health education to patients and their caregivers, covering disease progression and safety precautions. Formal informed consent will be obtained prior to the initiation of each specific therapeutic modality.

ETT training group

Prior to the intervention, participants will be briefed on the principles and safety precautions of the ETT training to alleviate anxiety and optimize compliance. Patients will be positioned supine on the tilt table, with the thorax, pelvis, and knees secured by safety straps. A support board will be utilized for upper limbs stabilization, while the lower limbs remain extended with the feet resting firmly against the footboard. Participants will be instructed to maintain a relaxed, neutral posture throughout the procedure.

The training will initiate at a tilt angle of 30°. Following an initial 15-min tolerance period, the angle will be increased in increments of 10–15°, as tolerated by the patient. Each session will last 30 min, performed once daily, 5 days per week. Both the tilt angle and duration will be progressively adjusted based on the patient’s functional recovery. The primary therapeutic goal is to achieve tolerance of a 90° vertical position for 30 min without adverse symptoms or discomfort.

For safety monitoring, hemodynamic and respiratory parameters, including systolic blood pressure, diastolic blood pressure, mean arterial pressure, heart rate, and oxygen saturation, will be recorded prior to each session, monitored continuously during training, and recorded again immediately upon completion of the session.

Sequential EECP - ETT training group

Participants in this group will receive EECP therapy followed by ETT training in a sequential manner.

EECP therapy will be initiated following standard equipment calibration and safety checks (including cuff integrity and system initialization). Electrodes will be positioned at designated precordial sites to ensure stable ECG triggering, and a digital plethysmographic pulse oximeter will be attached for real-time hemodynamic monitoring. Participants will be positioned supine, with pressure cuffs wrapped sequentially around the calves, lower thighs, and upper thighs/buttocks, ensuring the coccyx is correctly aligned.

EECP inflation pressure will start at the minimum effective level and be incrementally uptitrated to the target therapeutic range over 3–5 sessions, adjusted for individual subcutaneous fat and muscle mass. In this study, the target inflation pressure is 150 mmHg. Treatment efficacy will be optimized by adjusting the inflation/deflation pressure and timing to maintain a diastolic-to-systolic augmentation ratio (D/S ratio) > 1.2 and a diastolic-to-systolic area ratio (DP/SP ratio) of 1.5–2.0. Each session will last 60 min, though duration may be reduced based on patient tolerance. Training will be conducted 5 h per week for 7 weeks, totaling 35 sessions.

Electric tilt table training will be initiated exactly 15 min after the completion of each EECP session. Systolic and diastolic blood pressure, mean arterial pressure, heart rate, and oxygen saturation will be recorded before, during, and after both EECP and ETT training.

Safety considerations: Potential transient adverse effects associated with EECP and ETT training include lower-limb discomfort, skin erythema or abrasion at the cuff contact sites, transient headache, dizziness, nausea, excessive sweating, orthostatic intolerance, and syncope. All adverse events will be documented throughout the study and managed according to predefined safety procedures. Participants who develop serious or intolerable intervention-related adverse events (e.g., refractory orthostatic hypotension, persistent arrhythmias, decompensated heart failure, or syncope requiring medical evaluation) or new contraindications to EECP or ETT (e.g., incident venous thrombosis or progression of aortic regurgitation), as determined by the investigators, will discontinue the study intervention. Unless they withdraw informed consent, these participants will continue scheduled follow-up assessments according to the study protocol. Training (either EECP or ETT) will be immediately discontinued if any of the following clinical conditions occur: marked fatigue, acute pain, agitation, profuse sweating, palpitations, chest tightness or angina, dyspnea, heart rate ≥120 bpm or ≤40 bpm, systolic blood pressure >180 mmHg or <90 mmHg, respiratory rate ≥35 breaths/min, oxygen saturation <90%, new-onset arrhythmias, or dynamic ST–T segment changes. Standardized medical management will be promptly initiated.

### Assessment schedule and retention strategies

Baseline assessments will be performed upon enrollment. Post-intervention assessments will be conducted immediately following the completion of the 7-week treatment period. All scheduled evaluations will be executed according to the predefined study timeline and standardized protocols. To enhance participant adherence and ensure data integrity, the research team will implement a proactive engagement strategy. This includes longitudinal monitoring through bedside visits (for inpatients) and regular telephonic follow-ups (for discharged patients or caregivers). These interactions are designed to monitor recovery progress, mitigate potential attrition (dropout), and promptly address any concerns or queries regarding the study procedures. Measures to minimize missing data will include double-checking assessment records and maintaining flexible scheduling for follow-up evaluations.

### Outcomes

The outcome measures were selected to evaluate the potential clinical benefits of the sequential EECP-ETT strategy within a comprehensive rehabilitation program. As the proposed sequential intervention is intended to improve orthostatic tolerance and facilitate early verticalization, its potential benefits are expected to extend beyond immediate hemodynamic effects to multiple domains of functional recovery commonly affected after stroke. The primary outcome is neurological function at week 7, assessed by the NIHSS. NIHSS was selected as the primary endpoint because it comprehensively reflects overall neurological recovery, which is the ultimate goal of early stroke rehabilitation beyond immediate hemodynamic improvements. Secondary outcomes include the incidence of symptomatic OH, recorded continuously during all ETT training sessions throughout the 7-week intervention. OH is defined as a systolic blood pressure drop ≥ 20 mmHg, a diastolic drop ≥ 10 mmHg, or the onset of hypotensive symptoms within 3 min of tilting (30). Additional secondary outcomes, assessed at week 7 (Table 1), evaluate specific functional domains and hemodynamics, including motor function quantified by the FMA, balance function assessed by the BBS, swallowing ability via the MMASA, activities of daily living quantified by the BI, and noninvasive hemodynamic parameters, specifically cardiac index (CI), stroke volume (SV), and systemic vascular resistance index (SVRI).

**Table 1 tab1:** Outcome domains and measurement instruments.

**Outcome domain**	**Measurement instrument**	**T0**	**T1**
Primary outcome			
Neurological function	National Institutes of Health Stroke Scale	√	√
Secondary outcomes			
incidence of symptomatic orthostatic hypotension	Noninvasive blood pressure monitor and clinical observation	*	*
Motor function	Fugl-Meyer Assessment	√	√
Balance function	Berg Balance Scale	√	√
Swallowing function	Modified Mann Assessment of Swallowing Ability	√	√
Activities of daily living	Barthel Index	√	√
Noninvasive hemodynamic parameters	Thoracic electrical bioimpedance assessment system	√	√

T0 baseline, T1 post-intervention (week 7). *The incidence of symptomatic orthostatic hypotension is monitored continuously during each ETT training session rather than at discrete T0/T1 timepoints.

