## Background

Ischemic stroke remains a major public health challenge worldwide, characterized by high incidence, substantial disability, and considerable mortality (1, 2). While early systematic rehabilitation is essential for functional recovery, traditional motor therapies offer limited efficacy (3, 4). For bedridden patients, early verticalization is imperative to restore consciousness, activate musculature, and improve motor stability (5–7). Although the electric tilt table (ETT) training is a standard tool for verticalization, its utility is often constrained by orthostatic hypotension (OH) (8–11). OH is common during inpatient stroke rehabilitation, affecting nearly half of patients; symptomatic OH occurs in approximately one-third of patients (12). Because ETT training involves progressive verticalization, OH may be precipitated or exacerbated during training. Symptomatic OH is of particular concern because it may interrupt rehabilitation sessions, limit tolerance to early mobilization, and compromise rehabilitation progress (13). Given the lack of definitive treatments for OH, targeted pre-conditioning strategies are required to enhance orthostatic tolerance (14).

Enhanced external counterpulsation (EECP) is a noninvasive circulatory support technique that augments venous return and cardiac output, improving perfusion to the heart and brain (15–18). Beyond its established therapeutic benefits, EECP’s hemodynamic effects suggest potential as a pre-conditioning strategy. By stabilizing vascular tone and increasing systemic perfusion prior to verticalization, EECP may mitigate OH and improve tolerance to ETT training (19). However, evidence regarding the sequential integration of these modalities remains scarce.

Consequently, we hypothesize that the early sequential application of EECP followed by ETT training synergistically promotes neurological and functional recovery in patients with ischemic stroke. This study aims to evaluate the clinical feasibility, efficacy, and safety of this integrative approach. We will assess its impact on neurological, motor, balance, and swallowing functions, alongside activities of daily living and noninvasive hemodynamic parameters (Figure 1). If validated, this strategy could optimize rehabilitation efficiency, providing evidence for a safe and accelerated early recovery pathway in stroke patients.

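### The secondary outcome is called symptomatic orthostatic hypotension, but the only printed definition is of OH and is met by a silent pressure drop or by symptoms alone

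*Protocol article*

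**What the plan says.** The Outcomes section of the protocol article states: "Secondary outcomes include the incidence of symptomatic OH, recorded continuously during all ETT training sessions throughout the 7-week intervention". The Abstract (aim, secondary outcomes and intended conclusion), Table 1 and Table 2 use the same label, symptomatic OH.

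The only case rule follows in the same section. It defines OH, without the adjective. Two limbs rest on pressure: "OH is defined as a systolic blood pressure drop ≥ 20 mmHg, a diastolic drop ≥ 10 mmHg". A third limb needs no pressure reading at all: "or the onset of hypotensive symptoms within 3 min of tilting". The three limbs are joined by *or*. No sentence says what makes a case symptomatic, and the article does not list the hypotensive symptoms. Table 1 gives the instrument as "Noninvasive blood pressure monitor and clinical observation", with no rule for combining the two sources.

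The Background separates the two quantities. It puts OH at nearly half of stroke rehabilitation inpatients and adds that "symptomatic OH occurs in approximately one-third of patients". It singles out symptomatic OH because that form may interrupt sessions and hold back rehabilitation.

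**The concern.** The label and the rule describe different events. If the printed sentence is the outcome definition, a silent fall in pressure is counted as symptomatic OH, and so is a symptom with no fall in pressure. If the sentence defines only OH in general, then symptomatic OH has no definition at all. Either way, a statement at the end of the trial that the sequential strategy reduced symptomatic OH might rest on another quantity, and this is one of the stated aims.

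A second issue is bias. Under Randomization and blinding, participants and therapists know the allocation. The symptom limb lets a participant's report create an event with no pressure reading to support it. Blinding the assessors and analysts does not remove this.

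This is not a detail that an article leaves to a fuller document. The article prints a case definition, and the definition does not fit the name of the outcome.

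**Working it through.** **Plan's own figures.** The article gives no rate, effect or power for the OH outcome. Its sample size concerns NIHSS only: 2 × (1.960 + 1.282)² × 3.82² / 2.71² = 41.76, so 42 per group, as stated. Then 42/0.8 = 52.5, and the plan takes 52. Nothing below disputes this.

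**Who counts as an event.**

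| Pressure drop | Symptoms | Printed rule | Symptomatic OH in the usual sense |
|---|---|---|---|
| yes | yes | event | event |
| yes | no | event | not an event |
| no | yes, within 3 min | event | not an event |
| no | no | not an event | not an event |

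The rule and the label disagree in the two middle rows.

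**Size of the silent-drop row (illustration).** The inputs are the Background rates: any OH about 1/2, symptomatic OH about 1/3. Assume that every symptomatic case has a pressure drop.

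- Silent share of counted events: (1/2 − 1/3) / (1/2) = 1/3.
- Share that is truly symptomatic OH: (1/3) / (1/2) = 67%.
- If a further 5% or 10% of patients have symptoms without a drop (assumed; the article gives no figure): (1/3)/0.55 = 61%, or (1/3)/0.60 = 56%.

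**Effect on the comparison.** Assume that treatment halves symptomatic OH, from 1/3 to 1/6. Silent OH in the control arm is 1/2 − 1/3 = 1/6. Power is for a two-sided two-proportion test at 0.05, using the pooled variance under the null.

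| Outcome and assumption | Rates | Risk ratio | Power, 42 per arm | Power, 52 per arm |
|---|---|---|---|---|
| Symptomatic OH only | 1/3 v 1/6 | 0.50 | 0.421 | 0.501 |
| Printed rule, silent drops unchanged | 1/2 v 1/3 | 0.67 | 0.338 | 0.405 |
| Printed rule, silent drops also halved | 1/2 v 1/4 | 0.50 | 0.663 | 0.757 |

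The second row shows dilution. The third shows none, and has more power than symptomatic OH alone because there are more events. The sign of the change therefore depends on what EECP does to silent drops, which the article does not quantify.

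**The case against.** The strongest defence is that the sentence defines OH and that the word symptomatic adds a requirement of its own; Table 1 names both a pressure monitor and clinical observation. Staff may already be asking for both. On that reading silent drops are not counted, though symptoms without a drop still meet the printed definition. What stands of this is that the mismatch is certain only if the rule is applied as written. It does not rescue the definition, because the requirement is nowhere stated.

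A reader might infer four stronger points that the article does not support.

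- *That side effects of EECP will be counted as OH.* The safety paragraph lists "transient headache, dizziness, nausea, excessive sweating, orthostatic intolerance, and syncope" jointly for EECP and tilt-table training and does not attribute them to EECP. Tilting starts 15 minutes after EECP ends, and the symptoms must be hypotensive and arise within 3 minutes of tilting. Carry-over is possible but not shown.
- *That only the first tilt to 30° counts.* The Interventions section says: "Following an initial 15-min tolerance period, the angle will be increased in increments". Each increase can be read as a tilt, and the recording is continuous. The 3-minute phrase may also belong only to the symptom limb. This is an ambiguity, not an error.
- *That the treatment effect must be diluted.* The article's own rationale, that EECP supports venous return and perfusion, suggests that silent drops could fall too.
- *That this is a key secondary outcome.* It is listed first and belongs to the aim, but the article does not rank it.

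The Background rates also describe inpatient stroke rehabilitation in general, not cumulative incidence over 5 × 7 = 35 tilt sessions. Finally, requiring both components does not cure the bias: every event would then need a symptom or sign noted in an unblinded session.

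**Conclusion.** The point holds as a mismatch between an outcome's name and its only definition. Read literally, the printed rule is too broad in two directions: silent drops, and symptoms alone. The one-third share of asymptomatic events is illustrative. It rests on general rehabilitation rates and on every symptomatic case having a pressure drop. No direction can be given for the effect on the risk ratio or power: the risk ratio is 0.67 or 0.50, and power at 52 per arm is 0.405 or 0.757 against 0.501, according to whether silent drops respond to treatment. The documents do not establish that the reported rate is bound to differ from symptomatic OH, since staff may apply an unwritten symptom requirement, but they contain nothing that prevents it.

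This should be fixed because it bears on a stated aim. It does not touch the NIHSS primary outcome or the sample size, so it is not critical to the trial's main conclusion.

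**What to change.** Before unblinding, amend the outcome definition, for outcome counting only, as follows.

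- Symptomatic OH is a systolic drop of at least 20 mmHg or a diastolic drop of at least 10 mmHg, measured against the reading taken before tilting, **together with** at least one symptom or observed sign from a fixed list in the same time window. The Interventions section already has the pre-tilt reading recorded in both arms.
- State whether the 3-minute window applies to all limbs and whether it restarts at each increase in angle.
- Report separately any OH by blood pressure, which is the more objective measure, and symptoms without a drop.
- Document this as a mid-trial amendment. Enrolment began in July 2024, recruitment is ongoing, and the trial is expected to end in December 2026.
- Apply it to participants already treated only where session records allow. The Interventions and Data collection sections promise pressures before, during and after each session, but not readings or symptom times for each tilt step.

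The cost is an amendment, a derivation in the case report form and a check of existing records. Fewer events will be counted, and the outcome will still depend partly on symptoms seen or reported in unblinded sessions, which is why the pressure-only measure should stand beside it.

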### Participant timeline

Timeline for participants’ enrolment, interventions, and assessments is shown in Table 2.

**Table 2 tab2:** Time schedule of enrolment, interventions and assessments.

	**Study period**								
	**Enrolment**	**Allocation**	**Post-allocation**						
**Timepoint**	**-t1**	**t0**	**t1**	**t2**	**t3**	**t4**	**t5**	**t6**	**t7**
Enrolment									
Eligibility screen	X								
Informed consent	X								
Allocation		X							
Pre-treatment preparation									
Rehabilitation assessments			X						
Intervention									
A: Electric tilt table training			X	X	X	X	X	X	X
B: Sequential EECP-electric tilt table training group			X	X	X	X	X	X	X
Assessments									
National Institutes of Health Stroke Scale			X						X
Symptomatic orthostatic hypotension			X	X	X	X	X	X	X
Fugl-Meyer Assessment			X						X
Berg Balance Scale			X						X
Modified Mann Assessment of Swallowing Ability			X						X
Barthel Index			X						X
Noninvasive hemodynamic parameters			X						X
Safety			X	X	X	X	X	X	X

t1–t7 correspond to intervention weeks 1–7; EECP, Enhanced External Counterpulsation.

### Sample size estimation

Since there is limited literature evaluating the synergistic effects of this specific sequential intervention, the sample size was calculated based on our unpublished preliminary pilot study involving 18 participants (9 in each group). The mean NIHSS score at the end of the trial was 7.99 ± 3.82 in the ETT training group and 5.28 ± 2.16 in the sequential EECP-ETT training group, giving an expected difference (*δ*) of 2.71 with a standard deviation (*σ*) of 3.82. With a two-sided significance level (*α*) of 0.05, power (1–*β*) of 90%, and equal allocation (1: 1), the required sample size for each group was calculated using the formula:

$$n=\frac{2{\left(z_{\alpha }+z_{\beta }\right)}^{2}*\sigma^{2}}{\delta^{2}}$$

This calculation indicated that 42 participants per group were required (84 in total). Allowing for a 20% dropout rate, 52 participants will be recruited per group, for a total sample size of 104.

